## Abstract

**Introduction::**

Multimodality assessment of coronary artery lesions has demonstrated superior effectiveness compared to the conventional approach, for assessing both anatomical and functional significance of a coronary stenosis. Multiple imaging modalities can be integrated into a fusion imaging tool to better assess myocardial ischemia.

**Material and methods::**

The FUSE-HEART trial is a single center, prospective, cohort study that will assess the impact of a coronary artery stenosis on myocardial function and viability, based on advanced fusion imaging technics derived from Cardiac Computed Tomography Angiography (CCTA). Moreover, the study will investigate the correlation between morphology and composition of the coronary plaques and myocardial ischemia in the territory irrigated by the same coronary artery. At the same time, imaging parameters will be correlated with inflammatory status of the subjects. The trial will include 100 subjects with coronary lesions found on CCTA examination. The study population will be divided into 2 groups: first group will consist of subjects with anatomically significant coronary lesions on native coronary arteries and the second one will include subjects surviving an acute myocardial infarction. The vulnerability score of the subjects will be calculated based on presence of CCTA vulnerability markers of the coronary plaques: napkin ring sign, positive remodeling, spotty calcifications, necrotic core, and low-density plaques. 3D fusion images of the coronary tree will be generated, integrating the images reflecting wall motion with the ones of coronary circulation. The fusion models will establish the correspondence between plaque composition and wall motion in the subtended myocardium of the coronary artery. The study primary outcome will be represented by the rate of major adverse cardiac events related to myocardial ischemia at 1-year post assessment, in correlation with the degree of coronary artery stenosis and myocardial ischemia or viability.

The secondary outcomes are represented by the rate of re-hospitalization, rate of survival and rate of major adverse cardiovascular events (including cardiovascular death or stroke), in correlation with the morphology and composition of atheromatous plaques located in a coronary artery, and myocardial ischemia in the territory irrigated by the same coronary artery.

**Conclusion::**

In conclusion, FUSE-HEART will be a study based on modern imaging tools that will investigate the impact of a coronary artery stenosis on myocardial function and viability, using advanced fusion imaging technics derived from CCTA, sighting to validate plaque composition and morphology, together with inflammatory biomarkers, as predictors to myocardial viability.

## Introduction

1

### Background and rationale

1.1

Multimodality appraisal of coronary artery lesions in patients surviving an acute myocardial infarction (AMI) has demonstrated superior effectiveness in the complex evaluation of coronary circulation and residual lesions after percutaneous coronary interventions (PCI). Having a specificity of 85% for the diagnosis of coronary artery disease, Cardiac Computed Tomography Angiography (CCTA) offers also the possibility to evaluate the morphology and structure of atheromatous coronary plaques, at the same time providing a detailed view on the cardiac geometry using 3D reconstruction of acquired images.^[1–3]^

Coronary plaques were intensively studied using CCTA-based software for investigation of plaque morphology, which identified specific characteristics of vulnerable plaques that makes them prone to rupture. Usually, these vulnerable coronary plaques contain a necrotic core, spotty calcifications, have positive remodeling and a thin cap fibroatheroma.^[4–7]^

Different scores have been proposed for quantifying the impact of a coronary artery stenosis on the myocardial function. For instance, Duke Jeopardy score is a relatively simply scoring system that expresses the percent of the affected myocardium.^[8]^ The main reason for investigating the impact of a coronary stenosis on the myocardial contraction after myocardial infarction is to identify the presence of viable myocardium, which may restore its functionality and contraction after a proper revascularization procedure.^[9]^ However, in an animal experiment, Force et al. found that viable myocardium juxtaposed to widespread scarring may be unable to recover after proper revascularization due to tethering.^[10]^

This indicates that restoration of myocardial function is a more complex process, which depends not only on the patency of coronary artery and the degree of myocardial lesions, but also on the geometric and hemodynamic forces acting at the level of different myocardial areas.^[11]^

Cardiac Magnetic Resonance Imaging (CMRI) provides reliable information on wall motion, perfusion, volume and mass of the left ventricle, considered nowadays the golden standard for assessment and quantification of myocardial scar.^[12–14]^ Assessment of myocardial viability is mandatory to evaluate the ability of ischemic tissue to recover after revascularization therapy. The gold standard for the myocardial viability evaluation is fluorodeoxyglucose-positron emission tomography.^[15–18]^ However, while CMRI examination and especially the late gadolinium enhancement sequences can easily visualize the transmural extent of the viable and non-viable myocardium in a simultaneously way, the nuclear scintigraphy can only indirectly assess the viable myocardium.^[18]^

At the same time, in non-infarct patients, functional impact of a coronary stenosis is crucial for selection of the appropriate therapy, since not all anatomically-significant coronary lesions produce myocardial ischemia, while other non-significant lesions proved to be associated with significant ischemia in the territory supplied by that coronary artery. The concept of subtended myocardial mass, reflecting the myocardial area suffering from the deficit of blood supply, has been introduced recently as a result of development of new machine learning algorithms associated with CCTA technology, which automatically quantify the subtended myocardial mass irrigated by a coronary lesion.^[19]^ This may replace the conventional ways to assess functional significance of a coronary lesion, mainly based on fractional flow reserve (FFR) calculation.

Evaluation of coronary circulation by CCTA and myocardial viability by CMRI, as well as assessment of coronary artery stenosis by CCTA and functional significance with invasive FFR, involve two different imaging techniques for one assessment, both of them expensive and time consuming, significantly increasing the cost of the patient care.

We describe the study protocol of the FUSE-HEART trial, a single-center, prospective, cohort study which aims to investigate the impact of a coronary artery stenosis on myocardial function and viability, based on advanced fusion imaging techniques derived from CCTA.^[20]^

### Study objectives

1.2

The study primary objective is to investigate the impact of a coronary artery stenosis on myocardial function and viability, based on advanced fusion imaging techniques derived from CCTA.

The study secondary objective is to investigate the correlation between morphology and composition of atheromatous plaques located in a coronary artery and myocardial ischemia in the territory irrigated by the same coronary artery.^[20]^

## Methods/design

2

### Study design

2.1

This is a 2-year observational non-randomized clinical study, aiming to investigate the interrelation between the degree of coronary stenosis, plaque composition and myocardial ischemia. The period of 2 years consists of the 1-year follow-up period for major adverse cardiac events (MACE) events and the baseline screening.

### Ethics

2.2

The FUSE-HEART protocol was authorized by the Ethics Committee for Scientific Research of the Cardio Med Medical Center (certificate of approval: 23/19.12.2017) and by the local Ethics Committee for Scientific Research of the University of Medicine and Pharmacy George Emil Palade of Tirgu-Mures, Romania (certificate of approval: 353 from 13 December 2017). All study procedures were verified in order to fulfil with the Declaration of Helsinki of 1975, and all subjects will assume a signed consent.

### Study population

2.3

The study population will include 100 subjects with coronary lesions depicted by CCTA examination. The study population will consist in:

(1)patients with anatomically significant coronary lesions (at least 50% luminal narrowing) on native coronary arteries, or(2)patients surviving an acute myocardial infarction, revascularized or not.

In all patients, presence of vulnerability features in the atheromatous plaques will be studied and the vulnerability score will be calculated for each plaque, consisting in one point added for each of the following vulnerability markers: positive remodeling, napkin-rink sign, presence of low-density plaque or spotty calcium within the plaque. In addition, following 3D fusion of the images of the coronary tree with the images reflecting wall motion, the correspondence between plaque morphology and composition on one hand, and wall motion in the corresponding distribution territory of that coronary artery, will be studied based on fused models.^[20]^

The study will be conducted over a period of 2 years. Patient assessment will be performed at baseline and at 1 year, and the projected recruitment period will be 1 year.

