### Outcomes

2.8

The primary outcome of the study is to evaluate the rate of MACE events related to myocardial ischemia at 1-year post assessment, in correlation with the degree of coronary artery stenosis and myocardial ischemia or viability.^[20]^

The study secondary objective is to investigate the correlation between morphology and composition of atheromatous plaques located in a coronary artery and myocardial ischemia in the territory irrigated by the same coronary artery.^[20]^

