### Sample size

2.10

The trial sample size is represented by 100 subjects with anatomically significant coronary artery disease depicted by CCTA examination. The lot size estimation was done using the StatMate 2.0 software. A percent of 60% event-free study population was estimated for sample size calculation%, and a sample size of 50 subjects in each group is associated with a power of 90% for detection of an increase of 0.29 in MACE-free rates proportion, with a significance level (alpha) of 0.05 (two-tailed). Consequently, the study lot population including the 2 study groups of 50 patients each, was set at 100 patients.

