### Statistical analysis

2.11

The Graph Pad InStat 3.10 software will be used for statistical analysis, with a 5% level of significance. All data will be first checked for normality test. Continuous variables having normal distribution will be considered as mean ± standard deviation and will be compared using the t-test. Non-normally distributed data will be analyzed using the Mann-Whitney test. All the categorical variables, expressed in numbers and percentages, will be compared using the Fisher exact test.^[20]^

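### Plaques are scored individually and several can come from one patient, but the only tests named assume independent observations and the unit of analysis is not settled

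*Protocol article*

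**What the plan says.** All references are to the protocol article.

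- **2.3 Study population:** "the vulnerability score will be calculated for each plaque", with one point per vulnerability marker. The section then relates plaque morphology and composition to wall motion in the territory of that same artery.
- **1.2 Study objectives and 2.8 Outcomes:** the secondary objective relates plaque morphology and composition to "myocardial ischemia in the territory irrigated by the same coronary artery". The natural unit is the plaque, or the artery with its territory.
- **Inclusion criteria (under 2.3):** one qualifying lesion is the minimum, so several are allowed. The Discussion presents multivessel disease as a use of the method.
- **Abstract, Material and methods:** "imaging parameters will be correlated with inflammatory status of the subjects". The same paragraph speaks of a vulnerability score of the subjects, not of the plaques.
- **Discussion:** announces a biomarker sub-study relating systemic markers to local plaque features.
- **2.11 Statistical analysis:** normal data go to the t-test, "Non-normally distributed data will be analyzed using the Mann-Whitney test", and all categorical variables go to the Fisher exact test. No unit of analysis is given.

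**The concern.** Plaques and territories in one heart share the patient's risk factors, treatment and any earlier infarction, so their features and wall motion are likely to be correlated. The three named tests take each row as an independent observation. Applied to plaque rows, they use the wrong standard error.

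The case to worry about most is a blood marker. One hs-CRP, MMP-9 or IL-6 value per patient would be set against several plaques of that patient, and the analysis would count more independent information than it has. At stake are the secondary objective and the biomarker sub-study, where associations could be reported with p-values and intervals that do not mean what they claim.

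**Working it through.** **1. The plan's own figure, to see what it covers.** Section 2.10 states: "A percent of 60% event-free study population was estimated for sample size calculation"; "a sample size of 50 subjects in each group is associated with a power of 90" per cent; "for detection of an increase of 0.29 in MACE-free rates proportion"; alpha 0.05, two-sided. That is 60% against 60% + 29% = 89% MACE-free, 50 against 50 patients. Exact Fisher power, summed over Binomial(50, 0.60) × Binomial(50, 0.89), is 90.2%. The normal approximation gives 92.6% uncorrected and 88.6% with continuity correction. The stated 90% reproduces. It counts patients and MACE, so clustering of plaques does not touch it.

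**2. Inputs the article does not give.** Neither the number of plaques per patient (m) nor the ICC is stated. I assume m = 2 to 4 and ICC = 0.1 to 0.5, with 100 patients.

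**3. Exposure shared by all plaques of a patient** (biomarker or study group). The true variance exceeds the assumed one by the design effect DE = 1 + (m − 1) × ICC, and the true type I error is 2 × [1 − Φ(1.96/√DE)]. Lowest case: m = 2, ICC 0.1, DE = 1.1, 1.96/√1.1 = 1.87, giving 0.062. Highest case: m = 4, ICC 0.5, DE = 2.5, 1.96/√2.5 = 1.24, giving 0.215.

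| m | ICC 0.1 | ICC 0.3 | ICC 0.5 |
|---|---|---|---|
| 2 | 0.062 | 0.086 | 0.110 |
| 3 | 0.074 | 0.121 | 0.166 |
| 4 | 0.086 | 0.155 | 0.215 |

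At m = 3, the effective number of independent observations among 300 plaques is 300/DE = 250, 188 and 150. Simulation of a plain t-test on plaque rows (4000 replicates) agrees: 0.055, 0.083 and 0.111 at m = 2; 0.081, 0.120 and 0.161 at m = 3.

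**4. Plaque feature against its own territory** (the secondary objective). Here the exposure varies within the patient, so the DE above does not apply. I simulated the same t-test with a binary exposure cut from a normal variable whose within-patient correlation is 0.3 or 0.

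| m | Exposure correlation | Outcome ICC 0.1 | 0.3 | 0.5 |
|---|---|---|---|---|
| 2 | 0.3 | 0.055 | 0.057 | 0.064 |
| 3 | 0.3 | 0.051 | 0.060 | 0.067 |
| 2 | 0 | 0.048 | 0.047 | 0.051 |
| 3 | 0 | 0.052 | 0.053 | 0.046 |

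The simulation standard error near 5% is √(0.05 × 0.95/4000) = 0.003, so only the larger entries are clearly above nominal. A separate simulation of pooled Fisher tests (m = 3, 3000 replicates) gave 0.056, 0.067 and 0.094 when the latent within-patient correlations of the two variables were 0.5/0.3, 0.5/0.5 and 0.7/0.7. Marked inflation therefore needs strong clustering of both variables.

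**5. Pure within-patient contrast** (m = 2, one exposed and one unexposed territory per patient). The true variance is now smaller than assumed, by the factor 1 − ICC, and the type I error is 2 × [1 − Φ(1.96/√(1 − ICC))]: 0.039, 0.019 and 0.006 for ICC 0.1, 0.3 and 0.5. Simulation gave 0.035, 0.019 and 0.006. Here p-values are too large and real associations are missed.

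**The case against.** The strongest reply is that the article never says plaque rows enter these tests. Section 2.11 is one general paragraph without endpoint or unit. It fits a patient-level comparison of the two study groups just as well, and the abstract's subject-level score points that way. The named tests are two-sample comparisons, not correlation methods, so 2.11 may not be the whole plan for the secondary associations. An article also leaves much to a full protocol or analysis plan that is not shown.

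Much of this stands. A reader might infer that the plan commits to treating each plaque as a separate patient, or to repeating one blood value across plaques. The text does not say so, and any inflation is conditional on that choice. The values of m and ICC are assumptions, and patients with a single lesion add no clustering, so a lower average m would mean less inflation.

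It does not remove the point. Section 2.11 is not silent: it assigns all categorical variables, and continuous data generally, to these tests. Section 2.3 creates per-plaque variables of exactly that kind, and no rule reduces them to one value per patient. The abstract and 2.3 also disagree on whose score it is.

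**Conclusion.** The point holds in conditional form. The article defines plaque- and territory-level data, allows several per patient, names only tests for independent observations, and is inconsistent on the unit of the vulnerability score. If plaques or territories are the rows, the resulting p-values and intervals are invalid:

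- **Shared exposure** (biomarkers, study group): too small, with type I error about 6% to 22% for assumed m = 2 to 4 and ICC 0.1 to 0.5.
- **Plaque against own territory:** near nominal to slightly inflated, about 5% to 7% at an assumed exposure ICC of 0.3.
- **Purely within-patient contrasts:** too large.

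A reader might infer that p-values for the secondary objective are generally too small. The calculations do not support that, because the direction depends on how the exposure varies within patients. It would also be wrong to extend the point to the primary outcome: the MACE comparison and the sample size are at patient level and stand as they are.

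**What to change.** In 2.11, state the unit of analysis for each secondary and biomarker analysis, and make the abstract and 2.3 agree on whether the vulnerability score belongs to the plaque or the subject.

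For plaque- or territory-level associations, name either GEE with patient-clustered robust variance or a mixed model with a patient random intercept. For biomarkers, use that clustered model or one per-patient summary defined in advance. The maximum score is one such summary, but it tends to rise with the number of plaques, so the choice should be justified.

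The cost is wording and modest extra analysis work. If the software named in 2.11 does not fit these models, another package must be named. Intervals may widen or narrow. No extra patients, scans or visits are needed, and the primary MACE comparison and the 100 patients do not change.

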**Inclusion criteria:**

Subjects undergoing CCTA examination, with at least one coronary artery lesion producing a luminal narrowing > 50%Conscious subjects in order to sign and assume a paper-based consentSubjects at the age of maturity

**Exclusion criteria:**

Refusal or inability to sign the paper-based consentAllergy to iodine contrast agent used for CCTA acquisitionProved contraindications to CCTA evaluationIrregular or rapid heart rhythmPregnancy or lactationRenal dysfunction (dialysis or serum levels of creatinine>1.5 mg/dL)Malignant disease in the last 5 yearsLife expectancy less than 2 years

### Study settings

2.4

This clinical single center study will be runned in the Cardio Med Medical Center - Center of Advanced Research in Multimodality Cardiac Imaging, being funded by the Romanian Ministry of European Funds, the Romanian Government and the European Union, as part of the research grant number 103544 - Plaque IMAGE (contract number 26/01.09.2016), which was selected for funding following an international peer-review procedure within the national competition of research grants.^[20]^

### Study groups

2.5

One hundred subjects meeting the selection criteria will be divided into 2 groups, thus, subjects with anatomically significant coronary lesions (at least 50% luminal narrowing) on native coronary arteries (group 1), and subjects surviving an acute myocardial infarction, revascularized or not (group 2).^[20]^

### Study procedures and outcome assessment

2.6

The following data will be collected and recorded from all the subjects participating in the study: -baseline parameters of demography, medical history, cardiovascular risk factors, physical examination information, CCTA parameters, trans-thoracic echocardiography measurements, venous blood sample values, conventional 12-lead electrocardiography will be performed for all the subjects at baseline and follow-up.

#### Biomarkers assays

2.6.1

At baseline, electrochemiluminescent immunoassay (IMMULITE 2000 XPi Immunoassay System, Siemens, United States of America), biochemistry, blood count and NT-proBNP will be determined. Also, inflammatory status will be determined and analyzed at the Advanced Medical and Pharmaceutical Research Center of the University of Medicine and Pharmacy Tirgu-Mures, Romania, based on serum high sensitive C-reactive protein levels determined using immunoturbidimetric assay (COBAS INTEGRA 400 plus analyzer, Roche Diagnostics, Switzerland).

MMP-9 and Il-6 levels will be also evaluated using ELISA method (Dynex DSX Automated ELISA System, Dynex Technologies; IMMULITE 2000 XPi Immunoassay System, Siemens, United States of America).^[20]^

#### CCTA examination

2.6.2

All subjects will undergo a CCTA examination using a Siemens Somatom Definition 128 slices scanner (Siemens Healthcare GmbH, Erlangen, Germany). The acquired images will evaluate the coronary tree, especially the coronary stenoses, the presence of the plaques vulnerability markers such as: napkin ring sign, necrotic core, spotty calcifications, low density plaque, positive remodeling. Duke Jeopardy score will be calculated based on CCTA images.

#### Cardiac Transthoracic Echocardiography assessment

2.6.3

2D Echocardiography will be performed at baseline using Vivid E9 echocardiography system (General Electric Vingmed Ultrasound, Horten, Norway) for assessment of myocardial contractility. Moreover, all cardiac diameters, volumes and ejection fraction will be evaluated.

#### Fusion imaging protocol

2.6.4

Computational CT analysis will be performed using a Siemens SyngoVia software (Siemens Medical Solutions, Erlangen Germany), consisting in 3D reconstruction of the coronary arteries and myocardial motion.

Coronary plaques advanced analysis will be performed semi-automatically using an image algorithm which detects the vascular contour, on the same research software using the imagistic platform dedicated to the coronary analysis (SyngoVia Frontier Coronary Plaque Analysis, Siemens, Erlangen, Germany), and the coronary arteries will be individually reconstructed around their axis. The 3D images of the coronary tree will be superimposed on the 3D images of myocardial tissue, color-coded in accordance with the contractility level of each myocardial area. Figure 1 represents an illustration of the first prototype obtained as a result of fusing imaging, fusing images of the coronary tree with images of the corresponding myocardial regions irrigated by each coronary artery.

